### Blinding

Outcome assessors at follow-up will be blinded to the treatment condition of each participant when they assess the primary and secondary outcomes, but they may not be blinded in future follow-up due to disclosure of the treatment condition by the subject during the interview*.* To prevent this, follow-up duties will be done by five or more interviewers, and follow-up of a particular subject may be done by different interviewers. The biochemical validation will be done by a staff member who has not delivered the intervention and conducted the telephone follow-up. Yet all subjects will not be blinded, because they will receive the behavioural intervention.

### Statistical analyses

All data will be entered and analysed by SPSS for Windows version 20. The rate of quit attempts and 7-day point prevalence of abstinence will be assessed with the chi-square test and odds ratios of logistic regression. Continuous variables of perceived importance, confidence and difficulty to quit will be tested with repeated-measures ANOVA. Both intention-to-treat (assuming missing subjects have no changes) and complete case analyses will be done.

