**Fig. 1 Fig1:**
[figure not shown]
Flow of outreach interventions. *NRT* nicotine replacement therapy

**Table 1 Tab1:** Schedule of enrolment, interventions and assessments

	Study period					
	Enrolment	Allocation	Post-allocation			
Time point	Baseline	Baseline	1 week	1 month	3 months	6 months
Enrolment						
Eligibility screen	X					
Informed consent	X					
Allocation		X				
Interventions						
Intervention group		X				
Control group		X				
Assessments						
Socio-demographic	X	X				
Daily cigarette consumption		X	X	X	X	X
Intention to quit		X	X	X	X	X
Self-reported quitting outcomes			X	X	X	X
Perceived importance, confidence and difficulty to quit			X	X	X	X
Use of NRT			X	X	X	X
Biochemically validated quitting outcomes			X	X	X	X

*NRT* nicotine replacement therapy

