### Outcomes

The primary outcome is the proportion of any self-reported quit attempts (no smoking for at least 24 hours) in the past month at 1-month and 3-month follow-up. The secondary outcomes are self-reported 7-day point prevalence of abstinence at 1-month, 3-month and 6-month follow-up, perceived importance, confidence and difficulty to quit (scale 0–10) at all follow-up stages, proportion of using NRT in the past week or past month, and biochemically validated abstinence at 1-month follow-up.

At 1 week and 1, 3 and 6 months after recruitment, all subjects will be contacted by a trained interviewer via telephone for a survey of assessing these outcomes. After the survey, the interviewer will discuss any difficulties in quitting and using NRT with the subject. At least seven call attempts at different time points will be made before the subject is considered a loss to follow-up. Subjects who report no smoking in the past 7 days will be considered self-reported quitters. Self-reported quitters at 1 month will be invited to participate in a biochemical validation including measurement of exhaled carbon monoxide (CO) and salivary cotinine level by NicAlert® strips (http://www.nymox.com/default.action?itemid=45) near their residence. The criteria for validated abstinence were exhaled CO < 4 ppm and salivary cotinine < 10 ng/ml [33, 34].

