### Sample size determination

Since the RCT will generate preliminary estimates for effectiveness of the NRT sample, we propose the sample size as 50 for each arm (i.e. total sample size = 100). A similar RCT conducted by Jardin et al. [19] which evaluated the effectiveness of 2-week free NRT to help non-motivated smokers to quit smoking was used for the power estimation. The results showed that the 3-month quit attempt rate of receiving free NRT was significantly higher than for those who only received a quitline referral (32 % vs 16 %, *p* = 0.05). The relative risk (RR) is therefore determined (32 %/16 % = 2.0). Based on the RR of 2.0 and the 100 subjects, the power and type I error for detecting the difference using the Fisher’s exact test will be 69.7 % and 0.08. Based on our recent experience with the same recruitment method and setting, the successful recruitment rate was about 15.4 % (1254/8063). We therefore estimate we have to approach 650 smokers to achieve the target sample size.

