### Randomization

The individual randomization method by SNOSE will be used to ensure the allocation sequence is concealed from both ambassadors and participants before the group allocation [35, 36]. The primary investigator will prepare about 150 identical, opaque, sealed, A5-sized envelops, with a unique three-digit serial number on the cover of each envelope as an identifier. Half of the envelopes will each contain an eligibility form, an education card of NRT and an action plan for the intervention group. The remaining half will contain the same eligibility form and education card, and an action plan for the control group. After inserting the intervention materials in the envelopes, they will be shuffled and then numbered. When the subject consents to participate, the ambassadors will open one envelope according to the sequence of the serial number and assign the treatment condition based on the action plan.

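### No baseline covariates or ranking are stated for the quit-attempt analysis: prespecifying an adjusted logistic model as primary would be a modest, nearly free gain in efficiency

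*Protocol article*

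**What the plan says.** The primary outcome, in the Outcomes section, is binary: the "proportion of any self-reported quit attempts (no smoking for at least 24 hours) in the past month at 1-month and 3-month follow-up". The Statistical analyses section states that quit attempts and abstinence "will be assessed with the chi-square test and odds ratios of logistic regression". The chi-square test is the only hypothesis test named for these outcomes, and logistic regression appears as the source of odds ratios. The section does not say which is primary, and it neither lists nor excludes covariates.

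Table 1 marks "Intention to quit" and "Daily cigarette consumption" at baseline. The Randomization section describes about 150 envelopes, half for each arm; once filled, "they will be shuffled and then numbered". No stratification factor or block is described. The Sample size determination section says "we propose the sample size as 50 for each arm (i.e. total sample size = 100", and describes the aim modestly: "the RCT will generate preliminary estimates for effectiveness of the NRT sample".

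**The concern.** A chi-square test cannot use baseline information. Intention to quit is a natural predictor of a later quit attempt. The Background and Discussion expect recruits to differ in motivation, and motivation is the route by which the sample is meant to work. With unstratified allocation and 50 per arm, the arms can differ noticeably on intention by chance. A prespecified adjusted model uses the baseline values to remove that part of the noise.

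There is also a matter of choice. Two analyses are named without a ranking, and an adjusted logistic model would leave the covariates open. If they are fixed before the data are seen, the primary result cannot depend on which model is picked later. What is at stake is some precision in a small trial and a clear primary analysis. The validity of the test is not at stake.

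**Working it through.** **Inputs from the article.** 50 per arm; planning rates 32 % and 16 % (risk ratio 2.0); power and type I error given for Fisher's exact test ("test will be 69.7 % and 0.08"); two baseline variables in Table 1; no stratification.

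**Inputs assumed, because the article does not give them.** 40 % of subjects intend to quit; the odds ratio of intention for a quit attempt is 2, 4 or 6; the second covariate is not prognostic; tests are two-sided at 0.05.

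**1. The article's own power figure.** Normal approximation with pooled variance under the null:

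- Difference 0.32 − 0.16 = 0.16.
- Null standard error √(2 × 0.24 × 0.76 / 50) = 0.0854.
- Alternative standard error √((0.32 × 0.68 + 0.16 × 0.84) / 50) = 0.0839.
- One-sided 0.08: (0.16 − 1.405 × 0.0854) / 0.0839 = 0.477, power 68.3 %. This is close to the stated 69.7 %.
- Two-sided 0.08: 55.0 %, which does not reproduce it.
- Two-sided 0.05: 46.5 %; exact enumeration for the chi-square test gives 47.3 %.

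The base for the comparison below is therefore about 47 %.

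**2. Is the chi-square test valid?** Its exact size at nominal 5 % is 5.47 %, 5.08 % and 4.92 % at common rates of 16 %, 24 % and 32 %. Chance imbalance is already part of that error rate.

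**3. How large can chance imbalance be?** The standard deviation of the arm difference in the share intending to quit is √(0.4 × 0.6 × 2 / 50) = 0.098, or 9.8 points. The chance of a difference of at least 10 points is 36 %, and of at least 16 points 13 %.

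**4. Power with adjustment.** Simulation with 50 per arm and marginal rates of 32 % and 16 %. The adjusted test is the likelihood-ratio test for arm in a logistic model with both covariates (6,000 runs per row).

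| Intention odds ratio (assumed) | Chi-square | Adjusted | Raw gain |
|---|---|---|---|
| 2 | 46.5 % | 48.1 % | 1.6 |
| 4 | 46.9 % | 50.7 % | 3.8 |
| 6 | 47.8 % | 53.9 % | 6.1 |

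The Monte Carlo standard error of each power is about √(0.25 / 6,000) = 0.65 points. In a separate set of 8,000 runs with covariates that are not prognostic, the figures were 47.4 % and 48.2 %.

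**5. Correction for size.** Part of the raw gain is not real. Across the simulations the likelihood-ratio test rejected a true null in 5.2 % to 6.1 % of trials, and the chi-square test in 5.0 % to 5.6 %. With both calibrated to the same size, the gains are about 0 to 0.5 points (odds ratio 2), 2 to 3 points (odds ratio 4) and 4 to 5 points (odds ratio 6).

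**6. Where larger gains begin.** Expressed per standard deviation, with √(0.4 × 0.6) = 0.49, odds ratios of 2 and 6 are exp(0.49 × ln 2) = 1.40 and exp(0.49 × ln 6) = 2.41. Raw gains of about 7 and 13 points (47.0 % to 53.9 %, and 47.0 % to 60.2 %) needed odds ratios of 2.7 and 4.5 per standard deviation. The article gives no support for prognosis that strong.

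**7. Room in the model.** Expected events are 50 × 0.32 + 50 × 0.16 = 24. With arm and two covariates, that is 24 / 3 = 8 events per parameter.

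**The case against.** The strongest objection is that the article does not say the comparison is unadjusted. Logistic regression is named in the same sentence and is the usual vehicle for adjustment. Its covariates are commonly left to a full protocol or analysis plan, which is not shown. This stands: a reader might infer that the primary comparison is fixed as unadjusted, and the text does not support that. What remains is that the only named hypothesis test takes no covariates, and that the named model is given neither covariates nor primary status.

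A reader might also infer that chance imbalance would bias the result. It would not. The unadjusted test is valid in a randomised trial, and unstratified allocation leaves no design factor that the analysis must carry. This stands in full.

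Third, the gain is small and rests on assumed prognostic strength; moving from about 47 % to about 50 % power does not change what a preliminary trial can show. This stands as to size. But the change needs no new data, and practically nothing is lost if the covariates turn out not to be prognostic.

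Fourth, adjustment has costs: about 8 events per parameter, an odds ratio that becomes conditional instead of marginal, and slight size inflation of the likelihood-ratio test. These are real but manageable.

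Finally, planning on a risk ratio of 2.0 while naming odds ratios might be read as a contradiction. It is not: (0.32 / 0.68) / (0.16 / 0.84) = 2.47 is the same effect on another scale, and the risk ratio and risk difference follow from the two arm proportions.

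**Conclusion.** The point holds as a modest efficiency improvement. The article names an unadjusted test and an unspecified logistic model for quit attempts, ranks neither and states no covariates, although two plausible predictors are recorded at baseline. Nothing in this is wrong or contradictory. The size-calibrated gain is about 0 to 5 points of power on a base of about 47 %. It depends on three assumptions: an intention odds ratio between 2 and 6, 40 % of subjects intending to quit, and a two-sided 0.05 test at the planning rates. The lower end of that range is within simulation error of no gain. The documents do not support a claim of substantial lost power, of bias from imbalance, or of an inconsistent effect measure.

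**What to change.** In Statistical analyses, state that the primary analysis of quit attempts is a logistic regression on arm, baseline intention to quit and baseline daily cigarette consumption, using values recorded before the envelope is opened. Keep the chi-square test as the supportive unadjusted analysis.

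- Limit the model to these two covariates, each entered as a single term, given about 24 expected events.
- Report a standardised risk difference or risk ratio with its 95 % confidence interval beside the adjusted odds ratio, because that odds ratio is conditional.
- Name the test for arm. A Wald test avoids the slight size inflation of the likelihood-ratio test, but gives back a little of the nominal power gain.

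The cost is two or three sentences. Data collection, randomisation and sample size are unchanged. If a separate analysis plan already fixes the model and its covariates, a reference to it is enough.

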### Data quality control

Either the research nurse, the principal investigator or the research coordinator will coordinate the fieldwork at each recruitment site. All of the fieldwork and data management will be monitored by the other two co-investigators ([name] and [name]). The principal investigator will randomly select five intervention sites by simple individual randomization for checking of intervention fidelity. The research assistant and the investigators will have weekly meetings to review the study progress and procedures and to discuss any adverse events or dropouts. In view of the small sample size and short study period, a data monitoring committee, interim analysis and stopping guidelines will not be necessary. The data collection, management, analysis, interpretation and production of publications will be independent from the funding bodies and other competing interests. The trial results will be disseminated via journal publication and conference presentation, without exposing the identity of the trial subjects.

### Ethics, consent and permissions

The study protocol has been approved by the Institutional Review Board of the University of Hong Kong/Hospital Authority Hong Kong West Cluster (IRB reference number: UW 15-232). Written consent will be sought from all subjects to participate in this RCT, which will permit the investigators to disseminate the trial results and the study protocol via publications, without showing individual information.

All questionnaires will be stored in a cupboard with keys kept by the principal investigator and the research assistant only. The data will be kept for 10 years upon completion of the study. Electronic datasets of personal information and contact information will be encrypted and separated from the research dataset during the study period, and will be destroyed after the said storage period.

NRT has been proven an effective and safe aid for smoking cessation, which can be purchased over the counter in pharmacies or prescribed freely in smoking cessation clinics in Hong Kong. A common side effect of a nicotine patch is skin reaction. About 50 % of patients using the nicotine patch will experience a local skin reaction. The reaction is usually mild and self-limiting, but occasionally worsens over the course of therapy. Local treatment with hydrocortisone cream (1 %) or triamcinolone cream (0.5 %) and rotating patch sites may ameliorate such local reaction. In fewer than 5 % of patients, such reaction requires the discontinuation of the NRT. Other side effects are insomnia and/or vivid dreams. Common side effects of nicotine gum include mouth soreness, hiccups, dyspepsia and jaw ache. These effects are generally mild and transient, and can often be alleviated by correcting the patient’s chewing technique [13] or correcting the patient’s using habit. All subjects will be asked at telephone follow-up if they suffer from these side effects. If so, the counsellor will provide counselling on the usage. If the side effects are serious, the counsellor will ask them to cease usage.

## Discussion

Previous studies strongly supported that NRT is a safe and effective smoking cessation aid for smokers [7–9], but the low literacy reduces the using prevalence. Despite the widespread promotion of smoking cessation messages, an increase in the proportion of hardcore smokers and a reduction in the quit rate support that more effective methods for promoting cessation aids are needed [37]. The present RCT will assess whether providing a NRT sample is an effective health promotion strategy to enhance more quit attempts and increase abstinence. In addition to the effectiveness in quitting, the present RCT will yield more information on the adherence to the NRT sample, side effects and safety of NRT usage, and will also test whether the NRT sample and counselling increase quit motivation. These findings will provide insights towards enhancing smoking cessation services and constructing a larger trial to test the population effect in the near future.

A proactive approach with telephone ‘cold-calling’ or health records has been used by other studies, and was effective to increase abstinence [38, 39]. The present study is the first to extend this approach by directly initiating a face-to-face conversation with the smokers and then providing medication samples at smoking hotspots. These smokers may be less motivated to quit than those who seek cessation services through clinics or quitline. Because unmotivated smokers comprise a large proportion of smokers in Chinese communities, both in the China mainland and Hong Kong [3, 40], the present study will increase understanding on how to help these unmotivated smokers quit.

## Trial status

The recruitment is ongoing.

## Abbreviations

NRT, nicotine replacement therapy; RCT, randomized controlled trial; RR, relative risk; SNOSE, sequentially numbered, opaque sealed envelopes
